### Randomization

The randomization of GPs to the intervention or control arm will be conducted externally by the coordinating centre of the study in Greifswald. GPs consenting to participate are reported by the two regional coordinators to the study centre. The subsequent randomization will be conducted blockwise with blocks of four, six, and eight units length, to veil the possible allocation of the next GP.

### Ethics

The study is planned and conducted in accordance with medical professional codex and the Helsinki Declaration of 1996 as well as the German Federal Data Security Law (BDSG). Patients participate voluntarily. The study protocol was approved by the ethics committee of the University of Greifswald and Göttingen prior to the start of the study in March 2009. Patients receive written and spoken information about the main features of the study; i.e. about potential benefits for their health and potential risks prior to their consent and participation in the study. In case of acceptance, they sign the informed consent sheet. Patients are informed that they may cancel their participation at any time without disclosing reasons and without negative consequences to their medical care.

### Intervention

The intervention consists of the following elements: Firstly, a risk-factor screening, secondly, a risk tailored information and counselling, and thirdly a telephone/email consulting service for back pain related problems independent of risk group assignment. These elements are described subsequently:

#### Risk screening

After giving their informed and written consent to participate in the study patients will receive a brief self-rating risk screening inventory concerning yellow flags that are predictive of chronic back pain. The screening items are based on a German translation of the Örebro Musculoskeletal Pain Screening Questionnaire [41,42]. Ten out of the 25 items comprised by the instrument were selected for our investigation: pain intensity in the past week (one item), fear-avoidance beliefs (two items), depressive mood (two items), functional ability (four items), and body locations of pain (one item). The selection of these items was mainly based on previous findings concerning predictors for the course of back pain as outlined in the introduction. A brief instrument based on the selected domains was useful in predicting disability [15] and provided the conceptual background for our risk groups as described below.

The completed questionnaires will be returned to the practice nurse prior to the consultation and immediately analyzed to be available during consultation only in the intervention arm. Based on their screening responses patients in the intervention arm will be assigned to one of four risk groups (low/only physical/only psychological/physical and psychological). The low risk group comprises subjects without strong pain symptoms (defined by high intensity low back pain with functional limitations or multilocated pain) as well as low levels of depression and fear avoidance. The physical risk group comprises subjects with severe low back pain. Subjects that belong to this group experience high intensity and disabling back pain as well as pain in different body locations. The psychological risk group comprises subjects with strong low back pain and high levels of depression and fear avoidance. Subjects may be assigned to either one or both risk groups.

Apart from the subsequently described risk tailored intervention all patients receive treatment as usual. A national guideline for management of low back pain in primary care was published in 2001 [20].

#### Risk tailored intervention

The tailored interventions are based on the risk factor assignment.

#### Low risk group

Patients receive advice on staying active by the general practitioner and will be handed the back book. This is a German translation of the educational booklet developed by Burton et al [43]. This booklet fosters health related behaviours and was effective in reducing erroneous back related beliefs and fosters active health related behaviours. It argues against a biomechanical model by emphasizing psychological and social aspects of back problems. In addition patients receive additional information on local activities on physical exercise, sports and relaxation.

#### Physical risk group

In addition to the physicians' advices and the back book patients assigned to this group will be offered participation in a guideline based intervention group that consists of two meetings of 120 minutes duration each. The main focus of these manualized meetings will be: education on "back myths" and risk factors, introduction to self controlled exercise, and strategies to become and stay active. The groups will be conducted by experienced exercise therapists. The group size is limited to ten patients.

#### Psychological risk group

In addition to the physicians' advices and the back book patients assigned to this risk group will be invited to participate in a psychosocial risk factor group that comprises two additional meetings of 120 minutes duration each. These meetings will be conducted by psychologists with a specialization in pain treatment. Patients receive a manualized cognitive-behavioural intervention that focuses on pain and strain prone situations as well as on catastrophizing, depressive, and fear-avoidant cognitions. The group size is limited to six patients.

To monitor compliance an attendance list will be kept for every course. Patients receive an illustrated coloured handbook designed specifically for the purpose of this trial with information on all covered topics. All therapeutic sessions will be structured based on a written manual. All participating therapists will have attended a training session of four hours.

#### Telephone, email counselling

The aim of this counselling offer is to answer back pain related questions that usually cannot be handled during a normal consultation. Local study coordinators (usually physiotherapists) will take on enquiries and refer them to the collaborating physicians, psychologists, and sport scientists, as best suited. No diagnoses will be made during these contacts; neither will there be concrete therapeutic recommendations. A manual is authored to standardize responses given during the telephone/email counselling.

### Control group

Control patients will receive treatment as usual. They participate in the accompanying survey, including the baseline assessment, and the two follow-up surveys at six and twelve months. Furthermore, control patients complete the risk screening prior to their consultation. However, results of this screening will not be communicated to the doctor nor to the patient. Because control patients are recruited in different practices from intervention patients there is a low risk of cross-contamination.

### Hypothesis

Primary hypothesis: The risk tailored intervention is more effective in reducing disability (functional disability and sick leave) compared to treatment as usual.

Furthermore we hypothesize that a risk tailored intervention should promote self-management activities, lead to fewer negative pain-related cognitions and reduce the use of health care services because of non-specific back pain.

### Assessing Selection Bias

Non-response bias may threaten the validity of our results. Therefore all practices will document successful and failed recruitment attempts. Age and sex of patients who refuse to participate will be recorded. Drop-out to the follow up surveys will be statistically controlled based on the participants' responses at baseline as described in data analysis.

### Primary Outcomes

Two primary outcomes were chosen with a high importance for patients as well as for health care providers: Functional disability as measured with the Hanover Functional Ability Questionnaire [44] and days of sick at the second follow up after 12 months. The latter is in particular important for a monetary assessment of the benefits of the brief intervention program.

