**Figure 1 F1:**
[figure not shown]
**Back pain and related variables recorded at baseline and after 6 and 12 months**.

This sample size is based on a power analysis that accounted for an assumed drop-out of one third of the initial participants to the second follow up as well as for a loss of power due to correlated data within primary sampling units. Based on previous results in a GP intervention study [39], an intraclass-correlation of 0.025 is a plausible assumption for the target outcomes of our study. Given a final cluster size of on average 20 subjects the design effect will be approximately 1.5. To detect a difference in functional disability between intervention and control group at the second follow-up that corresponds to a Cohen's d effect size of 0.3 with a significance level of 5%, and a power of 80%, a final sample of 265 subjects in each study arm will be necessary. Assuming a total drop out rate of even 40% till the second and last follow up, the initial sample size of 600 subjects per study arm will suffice to detect the outlined effect.

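### Two primary outcomes share one hypothesis, but the 5% level and 80% power are set for functional disability alone and no either, both or ordered rule is fixed

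*Protocol article*

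**What the plan says.** The Primary Outcomes section of the protocol article states: "Two primary outcomes were chosen with a high importance for patients as well as for health care providers". The two are functional disability on the Hanover questionnaire and days of sick leave, both at the 12-month follow-up. The section gives sick leave its own purpose, the monetary assessment of the programme. The Abstract also lists both as primary.

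The Hypothesis section puts both into one primary hypothesis: "The risk tailored intervention is more effective in reducing disability (functional disability and sick leave) compared to treatment as usual".

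The sample-size paragraph in the Design section (below Figure 1) deals with one of them. For a standardised difference of 0.3 in functional disability at 12 months, it states: "with a significance level of 5%, and a power of 80%, a final sample of 265 subjects in each study arm will be necessary". It concludes that, even at 40% drop-out, "the initial sample size of 600 subjects per study arm will suffice to detect the outlined effect". It gives no effect size, distribution or power for sick-leave days.

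The Data analysis section describes a cross-sectional comparison at the last follow-up and longitudinal multilevel and GEE models. It gives no order of testing, no division of the 5%, and no statement of what counts as success on the primary hypothesis.

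**The concern.** The number of primary outcomes, the hypothesis that joins them, and the alpha and power behind the sample size are all fixed in this document. Together they do not determine when the primary hypothesis is supported.

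- **Either outcome suffices, each at 5%:** the primary claim has two chances to succeed, and its error rate exceeds the only level stated.
- **Both are required:** the error is controlled, but the stated 80% covers only half of the criterion.
- **Fixed sequence, functional disability first:** the 5% and 80% stand for that outcome as written, but no such order is stated.

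With a split result (one outcome significant, the other not), the text does not settle whether the primary hypothesis is supported. Choosing the rule after seeing the data would lose the error control.

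**Working it through.** **Inputs from the sample-size paragraph.** d = 0.3 (functional disability only), alpha 5%, power 80%. On clustering: "an intraclass-correlation of 0.025 is a plausible assumption for the target outcomes of our study" and "Given a final cluster size of on average 20 subjects the design effect will be approximately 1.5". Required completers 265 per arm; 600 per arm enrolled; drop-out one third, or 40% as the worse case. **Assumption:** the correlation between the two test statistics is not given, so a range of 0 to 0.9 is shown.

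**1. Reproduce the stated figure.**
- Design effect: 1 + (20 − 1) × 0.025 = 1.475, stated as about 1.5.
- n per arm before clustering: 2 × (1.960 + 0.8416)² / 0.3² = 174.4, rounded up to 175.
- 175 × 1.5 = 262.5. With the t-based n of 176, 176 × 1.5 = 264. With 1.475, 175 × 1.475 = 258.
- All are within 3% of 265, so the figure reproduces with a two-sided test. A one-sided 5% test gives 207 and does not, so 5% is read as two-sided.

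**2. Completers expected.** 600 × 0.6 = 360 per arm at 40% drop-out; 600 × 2/3 = 400 at one third.

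**3. Error rate if either outcome counts, each at two-sided 5%.** For independent tests, 1 − 0.95² = 9.75%. For correlated tests (bivariate normal):

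| Test correlation | At least one false significant result |
|---|---|
| 0 | 9.75% |
| 0.3 | 9.5% |
| 0.5 | 9.1% |
| 0.7 | 8.3% |
| 0.9 | 7.0% |

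These rates count significance in either direction. For false claims of benefit only, the independent case is 1 − 0.975² = 4.94%, against 2.5% for a single test, so the near-doubling is the same.

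**4. If both outcomes are required.** The error is at most 5%. Power depends on sick leave, for which no inputs exist. Two illustrations at 360 per arm and design effect 1.5 (effective 360 / 1.5 = 240 per arm):
- Sick leave also at d = 0.3 with the same ICC: joint power 82% at correlation 0 and 84% at 0.5.
- Sick leave at d = 0.2, independent tests: 0.2 / √(2/240) = 2.19; 2.19 − 1.96 = 0.23, power about 59%. Functional disability has 90.8%. Joint power is 0.908 × 0.59 ≈ 54%.

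Joint power can therefore lie on either side of 80%.

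**5. Functional disability at alpha 0.025 (first Holm step).**
- n before clustering: 2 × (2.2414 + 0.8416)² / 0.3² = 211.2. Then 211.2 × 1.5 = 317, or 212 × 1.5 = 318 after rounding up.
- Enrolment needed: 318 / 0.6 = 530, or 318 / (2/3) = 477, against 600 planned.
- Power at 360: 0.3 / √(2/240) = 3.286; 3.286 − 2.241 = 1.045, giving 85.2%. At 5%: 3.286 − 1.960 = 1.326, giving 90.8%.
- Power at 400 (effective 266.7): 88.9% at alpha 0.025, 93.4% at 5%.
- Sensitivity: a t-test on 38 df (40 practices − 2) at 360 per arm gives 82.5% at alpha 0.025. With 18 completers per practice, 80% survives up to a design effect of 360 / 212 = 1.698, an ICC of 0.698 / 17 = 0.041.

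**The case against.** The strongest reply is that this is a condensed article and the analysis plan is not shown. A multiplicity procedure commonly sits there, so its absence here would not by itself be a finding. That stands, and the point does not rest on it. It rests on what the article does fix: two primaries, one hypothesis, and a 5% level and 80% power attached to one of them. A plan that split alpha would depart from the 5% in the sample-size paragraph. A plan that required both would leave the 80% covering one of two conditions. Only a fixed sequence starting with functional disability fits that paragraph unchanged.

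Four stronger readings are tempting, and the documents do not support them:
- **That the type I error simply is nearly double.** This needs an either-outcome rule, which is nowhere stated. The *and* in the hypothesis equally allows a both-required reading. The two outcomes are also facets of disability, so some correlation is plausible, and 9.75% is the ceiling.
- **That the sample has room to correct both outcomes.** This is shown only for functional disability at d = 0.3 and ICC 0.025. Table 1 does not require employment, so sick-leave data may come from fewer patients.
- **That requiring both would push power below 80%.** Working step 4 shows that it could go either way.
- **That a split result could not be interpreted at all.** Each outcome could still be reported with its estimate and interval. What is undetermined is the status of the primary hypothesis.

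**Conclusion.** The point holds in conditional form. The document states two primary outcomes under one hypothesis and supports its 5% and 80% for one of them only.

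- **Either counts, each at two-sided 5%:** false-positive chance 7.0% to 9.75% for test correlations of 0.9 down to 0.
- **Both required:** error at most 5%, power unknown.

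A correction is affordable for functional disability: about 317 to 318 completers per arm needed at alpha 0.025, against 360 to 400 expected, with power of about 85% to 89%. This assumes d = 0.3, ICC 0.025, a design effect of 1.5 and normal-approximation tests. Nothing comparable can be said for sick leave from this document.

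**What to change.** Before outcome data are seen, state one rule in the protocol and the analysis plan:

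- **Holm** at an overall two-sided 5%: the smaller p-value is compared with 2.5% and, if significant, the other with 5%. Success is a significant benefit on at least one outcome.
- **Fixed sequence:** functional disability first at 5%, and sick leave at 5% only if the first is significant.

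If Holm is chosen, restate the power for functional disability at alpha 0.025: 317 to 318 completers per arm for 80% at design effect 1.5, and about 85% to 89% with 360 to 400 completers. Under either rule, say that the stated power does not cover sick leave. The restated paragraph should not say that 600 per arm was chosen to pay for multiplicity, since the document justifies that number by drop-out and clustering only.

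**Cost:** a few sentences and no extra patients. Under Holm, power for functional disability at the first step falls from about 91% to 85% at 360 per arm (design effect 1.5). The fixed sequence costs functional disability nothing, but a null result there rules out a confirmatory claim on sick leave.

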### Secondary Outcomes

A list of secondary outcomes is depicted in Table 2. Measures comprise the severity of back pain, depression, quality of life, fear-avoidance, catastrophizing, physical activities, and health care utilization. Effects of the intervention after 6 months and 12 months will be compared.

**Table 2 T2:** Outcomes and Instruments

Sociodemographic data	Deck R, Röckelein E. DRV-Schriften 1999, 16: 84-102. K.-H. Jöckel, B. Babitsch, et al. 1998, in: W. Ahrens et al. München: MMV Medizin Verlag. 7-38
Pain intensity, disability	Graded Chronic Pain Scale; Von Korff M, Ormel J, Keefe FJ, Dworkin SF. Pain 1992, 50: 133-49.
Functional capacity	FFbH -R; Kohlmann Th, Raspe H. Rehab 1996, 35: I-VIII.
Quality of life	SF 12; Gandek et al. J Clin Epidemiol. 1998, 51:1171-8
Use of medical services for LBP	Core set items of the German Back Pain Research Network
Depression	PHQ-D; Gräfe K, Zipfel S, Herzog W, Löwe B. Diagnostica 2004, 50(4):171-181.
Fear avoidance beliefs	FABQ; Pfingsten M, Kröner-Herwig B, Leibing E et al. European Journal of Pain 2000, 4: 259-266.
Physical activity, use of health promoting services	Wagner, P, Singer, R (2003). Sportwissenschaft 33 (4), 383-397.
Catastrophising	FSS; Flor, H., Behle, D. B., und Birbaumer, N. (1993). Behaviour Research and Therapy, 31, 63-73.

Additionally, participation in the counselling groups and telephone/email contacts will be documented.

### Data analysis

Baseline and follow up data will be presented using common parametric and non-parametric descriptive statistics. In addition to cross-sectional analysis to compare the control and intervention group at the second and last follow up, longitudinal analysis will use multilevel regression and generalized estimation equating (GEE) models with the outcome variables as outlined above. Non-response and drop out will primarily be accounted for by calculating statistical weights, or by conducting complete case analysis under the missing at random assumption, as appropriate. Comparisons predominantly concern the entire intervention group vs. the control group. A time vs. treatment group interaction will be computed to assess the benefits of the brief risk tailored assessment vs. treatment as usual.

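### Missing at random does not by itself justify the 12-month complete-case analysis, and the described drop-out control does not mention the 6-month data

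*Protocol article*

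**What the plan says.** All references are to the protocol article.

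- **Data analysis** plans a cross-sectional comparison at the last follow-up, plus longitudinal multilevel regression and GEE models with a time by treatment interaction. Non-response and drop-out are to be handled primarily by statistical weights, "or by conducting complete case analysis under the missing at random assumption, as appropriate".
- **Assessing Selection Bias** states: "Drop-out to the follow up surveys will be statistically controlled based on the participants"; the sentence goes on to name their baseline responses and to point to the data analysis section.
- **Design**, in the power paragraph below Figure 1, assumes that one third of patients are lost by the second follow-up. It then checks a worse case: "Assuming a total drop out rate of even 40% till the second and last follow up".
- **Design** and **Primary Outcomes** place measurements at baseline, 6 and 12 months, with both primary outcomes (functional disability and sick leave) read at 12 months.

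**The concern.** Missing at random lets 12-month drop-out depend on anything that was observed, including a patient's 6-month disability and study arm. Under that assumption the patients who return at 12 months can be a selected group, and selected differently in each arm. A complete-case comparison is protected only when drop-out is completely random or depends solely on covariates in the model. The 6-month outcome comes after randomisation, so it cannot simply be added as a covariate without changing the effect being estimated. Unweighted GEE has the same limit. Weights built from baseline answers also miss selection that runs through the 6-month state.

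The justification given therefore does not support the method it is attached to. What is at stake is bias in the primary comparison. Only the intervention arm receives screening feedback, group sessions and a counselling service, so drop-out that works differently by arm is plausible, though the article does not assert it.

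**Working it through.** **1. The plan's own figure.** Inputs from Design: "corresponds to a Cohen's d effect size of 0.3", "with a significance level of 5%, and a power of 80" per cent, "an intraclass-correlation of 0.025 is a plausible assumption" and a cluster size of 20. Two-sided, n = 2 × (1.96 + 0.84)² / 0.3² ≈ 175 per arm (176 by t-test). The design effect is 1 + 19 × 0.025 = 1.475, rounded in the plan to 1.5. Then 175 × 1.5 = 262.5 and 176 × 1.5 = 264, so the stated 265 reproduces.

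**2. What attrition leaves.** 600 × 2/3 = 400 and 600 × 0.60 = 360 per arm, with power of about 94% and 92%. The planned losses do not threaten power. The open question is bias.

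**3. Assumptions for an illustration (none is in the documents).** Functional disability has SD 1, and the true benefit is 0.30 SD at 6 and 12 months. Correlations are 0.5 (baseline to 6 months), 0.6 (6 to 12 months) and 0.45 (baseline to 12 months). Between 6 and 12 months, the log-odds of drop-out rise by b = 0.5 per SD of 6-month disability in one arm and are unrelated to it in the other. Any loss before month 6 is random and equal in both arms.

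**4. Formulas.** Let π be the late drop-out proportion among patients seen at 6 months and p the individual probability.

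- Shift in mean 6-month score among completers: S = b × E[p(1−p)] / (1−π), with E[p(1−p)] ≈ π(1−π) − [b π(1−π)]².
- Complete-case bias: 0.6 × S.
- Bias with baseline-only weights: about (0.6 − 0.5 × 0.45) × S = 0.375 × S.

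**5. Numbers.** If half of the total loss T falls before month 6, then π = (T/2)/(1 − T/2), which is 0.20 for T = 1/3 and 0.25 for T = 0.40.

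| Total loss | Share before month 6 | π | S | Complete-case bias (SD) | Baseline-weight bias (SD) |
|---|---|---|---|---|---|
| 1/3 | none | 0.333 | 0.157 | 0.094 (31%) | 0.059 (20%) |
| 40% | none | 0.40 | 0.188 | 0.113 (38%) | 0.071 (24%) |
| 1/3 | half | 0.20 | 0.096 | 0.058 (19%) | 0.036 (12%) |
| 40% | half | 0.25 | 0.119 | 0.071 (24%) | 0.045 (15%) |

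If the arm concerned is control, the effect shrinks. Complete cases give about 0.21, 0.19, 0.24 and 0.23 down the rows, and baseline weights about 0.24, 0.23, 0.26 and 0.25 to 0.26. If it is the intervention arm, the effect is inflated by about the same amounts. Large-sample simulation agrees with the table to within about 0.005 SD. In it, an analysis using baseline and all observed 6-month values returns 0.30 in every row.

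**6. Sensitivity.**

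- Same mechanism and rate in both arms: bias about 0 for every method.
- Drop-out dependent on baseline only, alike in both arms: about 0.
- Slopes 0.5 and 0.25 instead of 0.5 and 0, all loss late: complete cases about 0.25 (bias 15 to 19%).
- Three quarters of the loss before month 6: complete cases about 0.26 to 0.27.
- Opposite slopes of 0.5, all loss late: complete-case bias 64 to 77%.
- No true effect, intervention-arm slope 0.5, all loss late: complete cases show an apparent benefit of about 0.10 to 0.11.

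**The case against.** A reader might infer that attrition will distort the 12-month effect by a third. The documents do not support that figure. They give no between-visit correlations, no drop-out mechanism and no difference in drop-out between arms. A third arises for unadjusted complete cases when the mechanism works in one arm only and all loss comes after the 6-month survey. The stated 40% is a cumulative total, so some of it falls earlier, and those patients have no 6-month value to use.

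Nor does a third describe the weights, which the plan lists first. In the same scenario they lose about a fifth to a quarter, and complete cases adjusted for baseline do about as well as the weights.

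A reader might also infer that the plan restricts its correction to baseline answers. The selection-bias section names baseline responses but does not say that nothing else will be used, and the data analysis section does not list the weight variables.

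Finally, the multilevel regression already planned would be valid under missing at random if correctly specified and fitted to every available value. It is therefore too strong to say that every stated method leaves the bias in.

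These limits all stand. So does the reminder that this is a condensed article: the weight-model details, the rule behind the choice of method and further sensitivity analyses may sit in an analysis plan that is not shown, and their absence is not counted here. What remains is a method that the article does name, with a justification that does not support it.

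**Conclusion.** The point holds in limited form. Missing at random is not a sufficient reason for a 12-month complete-case comparison or an unweighted GEE, and the described drop-out control does not mention the 6-month wave that the trial collects.

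The size is conditional. It is about zero if drop-out acts alike in both arms. Under the assumptions in step 3, with none to half of the loss before month 6, it is about 19 to 38% of a 0.30 SD effect for unadjusted complete cases and about 12 to 25% for baseline-only weights, in either direction. Milder mechanisms or more early loss give less, and stronger ones more. The illustration concerns functional disability. The same logic applies to sick leave, but the documents give no figures from which to size it.

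**What to change.** - State that the primary 12-month comparison is the already planned multilevel model, fitted by likelihood to all available baseline, 6- and 12-month values. It should have a practice random effect, model the correlation between a patient's repeated values, and not be restricted to complete cases.
- If weights or GEE are used, fit the weights by arm and include the 6-month outcome where it was observed.
- Move complete-case analysis to a sensitivity analysis, and drop the statement that missing at random justifies it.

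The cost is analysis wording and modest programming. The 6-month data are already part of the planned collection.
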